#### ***Interim analysis***

An interim analysis is planned after the follow up data of the first 150 women that have been included is obtained. The interim analysis will be performed by an independent person and results will be reported to a data safety and monitoring committee (DSMC) for safety and relevance. As an indication, the trial will be stopped if there is a significant difference in the primary outcome, i.e. a poor neonatal outcome, at p < .005 (2-sided). However, the DSMC is free to make its own judgment.

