**Methods/Design:**

The Apostel III trial is a nationwide multicenter randomised controlled study. Women with threatened preterm labour (gestational age 25 – 34 weeks) defined as at least 3 contractions per 30 minutes, and 1) a cervical length of ≤ 10 mm or 2) a cervical length of 11-30 mm and a positive Fibronectin test or 3) ruptured membranes will be randomly allocated to treatment with nifedipine or atosiban. Primary outcome is a composite measure of severe neonatal morbidity and mortality. Secondary outcomes will be time to delivery, gestational age at delivery, days on ventilation support, neonatal intensive care (NICU) admittance, length admission in neonatal intensive care, total days in hospital until 3 months corrected age, convulsions, apnoea, asphyxia, proven meningitis, pneumothorax, maternal side effects and costs. Furthermore, an economic evaluation of the treatment will be performed. Analysis will be by intention to treat principle. The power calculation is based on an expected 10% difference in the prevalence of adverse neonatal outcome. This implies that 500 women have to be randomised (two sided test, β 0.2 at alpha 0.05).

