### Procedures, recruitment, randomization and collection of baseline data

The study will be a nationwide multicentre randomised controlled trial conducted within the Dutch Obstetric Consortium. The Dutch Obstetric Consortium is a research collaboration of obstetric clinics in the Netherlands. All 10 Dutch perinatal centres with NICU facilities will participate in the trial. In addition, 10 large teaching hospitals in the Netherlands and 2 perinatal centres in Belgium will participate in this trial.

Eligible women will be identified by the staff and/or local research coordinator of the participating hospitals. After counselling and reading the patient information form, patients will be asked for written informed consent. We will provide patient information in Dutch and English. After informed consent, baseline demographics, obstetric and medical history of patient will be entered in a web-based database, which will also facilitate randomisation. Randomisation will be performed by a web based computerized program using permuted-block randomisation. Randomisation allocation will be in a 1:1 ratio for Nifedipine or Atosiban, block size will be 4.

As this is a comparison of oral medication and intravenous medication, and as both group are treated with active medication, the study will not be blinded.

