### Statistical issues

#### ***Sample size***

The sample size is calculated based on a 10%- reduction of the composite poor neonatal outcome from 25% in the atosiban arm to 15% in the nifedipine arm. With a beta of 0.2 and alpha of 0.05 we have to randomize 500 patients (250 in each arm).

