### Data safety monitoring committee

Serious Adverse Events (SAEs) and Suspected Unexpected Serious Adverse Reactions (SUSARs) will be reported to a Data Safety Monitoring Committee (DSMC). The DSMC can decide to perform an extra interim analysis and, if indicated, terminate the trial prematurely.

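### An indicative p < .005 look at 150 of 500 women, followed by a final test at an unadjusted 0.05, gives an overall two-sided error of about 0.053, and extra looks have no stated level (minor)

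*Protocol article*

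**What the plan says.** All references are to the protocol article.

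- **Sample size**: the composite is expected to fall "from 25% in the atosiban arm to 15% in the nifedipine arm". The error rates and the resulting size come next in that section: "With a beta of 0.2 and alpha of 0.05 we have to randomize 500 patients (250 in each arm"). The abstract adds that the test is two-sided: "This implies that 500 women have to be randomised (two sided test, β 0.2 at alpha 0.05").
- **Data analysis**: the primary outcome is reported as rates, relative risks with 95% confidence intervals, and numbers needed to treat. No reduced final level is mentioned.
- **Interim analysis**: "An interim analysis is planned after the follow up data of the first 150 women that have been included is obtained". As an indication, the trial stops for a "significant difference in the primary outcome, i.e. a poor neonatal outcome, at p < .005 (2-sided"). The results go to the committee for safety and relevance, and the rule is not binding: "However, the DSMC is free to make its own judgment".
- **Data safety monitoring committee**: "The DSMC can decide to perform an extra interim analysis" and may end the trial early. The timing, outcome and significance level of such an analysis are not given.

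**The concern.** A two-sided comparison of the primary outcome that can stop the trial gives a first chance of a false positive. If the full 0.05 is then used again at the end, the two chances together exceed 0.05. The interim report is described as being for safety and relevance, but the criterion is a two-sided test of the primary outcome, so it can stop the trial for benefit of either drug as well as for harm.

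At stake is how a borderline final result is read. A final p-value between about 0.047 and 0.05 would be called significant at a level that the two-look design does not quite deliver. The optional extra analysis adds exposure that cannot be sized from the article, because no level is attached to it.

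**Working it through.** **Inputs from the article.** Event rates 25% and 15%; two-sided alpha 0.05; beta 0.2; allocation 1:1; 250 per arm; interim after 150 of 500 women, so information fraction t = 150/500 = 0.30; interim level two-sided .005.

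**Inferred input.** Final level 0.05. No sentence states it. The inference rests on the design alpha, the 95% intervals and step 1.

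**Step 1: reproduce the plan's figure.** Pooled two-proportion formula with mean rate 0.20:

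n per arm = [1.960 × √(2 × 0.20 × 0.80) + 0.842 × √(0.25 × 0.75 + 0.15 × 0.85)]² / 0.10² = [1.960 × √0.32 + 0.842 × √0.315]² / 0.01 = 249.98, rounded up to 250.

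This matches the stated 500 in total, with nothing set aside for an interim look. With a continuity correction the formula gives 270 per arm (540), which does not match.

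**Step 2: overall error with the planned look.** Under no difference, the interim and final statistics Z1 and Z2 are approximately bivariate normal with correlation √0.30 = 0.548. The bounds are 2.807 (p = .005) and 1.960 (p = .05).

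- P(|Z1| > 2.807) = 0.0050
- P(|Z2| > 1.960) = 0.0500
- P(both) = 0.0019
- Overall error = 0.0050 + 0.0500 − 0.0019 = **0.0531**

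Exact binomial enumeration with 75 and then 250 per arm, using the uncorrected chi-square test, gives 0.0527 to 0.0532 at common event rates of 15%, 20% and 25%.

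**Step 3: final level that holds 0.05.** Keep the interim bound and solve 1 − P(|Z1| < 2.807, |Z2| < c) = 0.05. This gives c = 1.988, that is p < **0.0468**. The matching interval has coverage 1 − 0.0468 = 95.3%.

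**Step 4: power at 250 per arm.** Single final test: Φ{[0.10 × √250 − z × √0.32] / √0.315}.

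| Final level | z | Single final test | Counting interim crossings as well |
|---|---|---|---|
| 0.05 | 1.960 | 80.0% | 80.2% |
| 0.0468 | 1.988 | 79.2% | 79.4% |

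Under 25% versus 15%, the chance of crossing at the interim is about 10%. An interim crossing counts as a rejection, so the planned look adds slightly to power. The small loss comes only from lowering the final level.

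**Step 5: one extra look.** The article gives neither time nor level, so both are assumptions here. The .005 look at t = 0.30 and the final 0.05 are kept.

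| Assumed time of extra look | Overall error, extra look at .005 | Overall error, extra look at .05 |
|---|---|---|
| t = 0.5 | 0.0545 | 0.0842 |
| t = 0.6 | 0.0542 | 0.0812 |
| t = 0.7 | 0.0537 | 0.0777 |

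**Step 6: a stricter interim level instead.** An interim level of .001 with 0.05 at the end gives 0.0505. That is closer to 0.05 but does not hold it.

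**The case against.** The strongest case against the point has five parts.

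1. *The excess is negligible.* It is 0.3 percentage points, and the article names no test for the primary outcome. With a continuity-corrected test the overall error would be about 0.038 to 0.041, below 0.05. The size of the excess stands as small. The corrected test is not what the sample size points to, since 500 reproduces only without the correction.
2. *The final level is inferred.* This stands. The full protocol, analysis plan or committee charter may set a lower final level. The point is therefore conditional, and the absence of such detail from a journal article is not itself a fault. What can be said is that the figures printed in the article, taken together, do not deliver 0.05.
3. *The stopping rule is only a guide.* This also stands. If the committee sometimes continued after a crossing, the error would lie between 0.05 and 0.0531. The same freedom allows stopping on weaker evidence, which would raise it.
4. *Power.* A reader might infer that the stated 80% is lost because of the interim look. The documents do not support that: power under the design as written is about 80%.
5. *Extra looks.* A reader might infer that the provision for an extra analysis inflates the error substantially. That holds only if such a look compares the primary outcome and is judged at an unadjusted .05. Nothing in the article says so. The provision stands beside the reporting of serious adverse events, names no outcome, and the only level given anywhere for an interim look is .005, at which the error stays near 0.054.

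**Conclusion.** The point holds as a minor one. If the p < .005 guide at 150 of 500 women is followed and the final test uses 0.05, the overall two-sided error is about 0.053 against the stated 0.05. This assumes an uncorrected test, an information fraction of 0.30 and an unadjusted final level. The sample size of 500 is correct for the stated inputs. The optional extra analysis is the looser end: its effect ranges from almost nothing to about three percentage points (0.0842 − 0.0531 = 0.031 at most in the cases examined), depending wholly on a level that the article does not give.

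**What to change.** Add two statements to the statistical section.

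1. The final primary comparison is tested at two-sided p < 0.0468, with a matching 95.3% confidence interval for the relative risk. Power at 500 women is then about 79%.
2. Any extra interim analysis that compares the primary outcome uses an alpha-spending boundary, and the final level is recomputed from the alpha that remains.

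If a fuller document already fixes a final level, it is enough to cite it and bring the stated alpha and interval into line.

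The cost is two sentences and under one point of power (80.0% to 79.2% as a single test; 80.2% to 79.4% counting interim crossings). No extra women are needed; restoring 80% on the single-test formula would take about 510. Moving the interim guide to .001 should not be presented as holding 0.05, because it leaves 0.0505.

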### Data safety monitoring committee

Serious Adverse Events (SAEs) and Suspected Unexpected Serious Adverse Reactions (SUSARs) will be reported to a Data Safety Monitoring Committee (DSMC). The DSMC can decide to perform an extra interim analysis and, if indicated, terminate the trial prematurely.

### Economic evaluation

We plan an economic evaluation of the costs and health effects of nifedipine and atosiban. The economic evaluation will be set up as a cost-effectiveness analysis (CEA) in which we will calculate the cost per prevented case of poor neonatal outcome. To evaluate cost-effectiveness within a long term horizon, downstream costs associated with poor neonatal outcome are estimated, and included in the analysis as a cost-to-benefit ratio. In a cost-utility analysis, with QALYs calculated from average life expectancy and utilities for severe neonatal morbidity, the incremental cost-effectiveness will be expressed as costs per QALY gained. In sensitivity analyses, the impact of parameter uncertainty and stochastic uncertainty is assessed, and the results are visualized in cost-effectiveness planes and cost-effectiveness acceptability curves.

In our economic analysis, we distinguish three cost stages (antenatal stage, delivery/childbirth stage and postnatal stage), and three cost categories: 1) direct medical costs i.e. all costs in the health care sector 2) direct non-medical costs i.e. costs outside the health care sector that are affected by health status or health care, and 3) indirect costs of the pregnant woman and her partner, for example costs of sick leave. For each stage and cost category, costs are measured as the volumes of resources used multiplied with appropriate valuations based on national reference prices, cost-per-unit estimates, or reimbursement fees.

Volumes of health care resource use are measured alongside the clinical study as part of the CRF as well as with questionnaires. Questionnaires will be based on the iMTA Medical Consumption Questionnaire (MCQ) and the Productivity Costs Questionnaire (PCQ) to collect data regarding health care consumption (e.g. number of GP contacts or outpatient visits, hospital admissions, and drug use), travel and time costs and productivity loss during follow-up at 6-month intervals. These questionnaires will be adapted to include only resources relevant to this study, and to document absence from paid work by the partners.

For an evaluation from a societal perspective, valuations of direct medical resources are estimated comprising ‘true economic’ costs, i.e. including shares of fixed costs and hospital overheads. Dutch reference prices are used where available. Otherwise, costs per unit are estimated for at least one teaching and one non-teaching hospital. Calculations based on reimbursement fees is added to our analysis to represent the payers perspective.

Indirect costs are quantified but remain unvalued. Study-specific costs are excluded from analysis.

### Ethical considerations

This study has been approved by the ethics committee of the Academic Medical Centre Amsterdam (Reference number MEC AMC 09/258) and by the boards of management of all participating hospitals. This trial is registered in the Dutch Trial Register, NTR 2947, http://www.trialregister.nl, date of registration: June 20^th^ 2011.

## Discussion

Preterm birth is an important cause of neonatal morbidity and mortality. Outcome of preterm infants can be improved and health care consumption and costs reduced by postponing delivery for 48 hours with tocolytic agents to allow maximal effect of maternal steroid administration and transportation of the mother to a centre with NICU facilities. The optimal type of tocolytic drug should improve neonatal outcome, be effective in delaying delivery, and safe for both mother and fetus. This trial will provide evidence on these subjects on the tocolytic drugs nifedipine and atosiban.

## Abbreviations

NICU: Neonatal intensive care unit; CRF: Case report form; BPD: Bronchopulmonary dysplasia; PVL: Periventricular leucomalacia; NEC: Necrotising enterocolitis; SAE: Serious adverse events; SUSAR: Suspected unexpected serious adverse reactions; DSMC: Data safety and monitoring committee.
